**Study hypothesis:** 1. Copeptin will improve the diagnostic accuracy to diagnose sodium imbalances as compared to routinely used markers 2. Copeptin will be a reliable prognostic tool, dependent or independent of sodium imbalance, to predict short-term (i.e. in-hospital) and medium-term (i.e. 3 months) clinical outcome in stroke patients. Further other biomarkers will be measured to assess prognostic values.

**Analysis:** Our sample size consideration is based on the second prognostic question to predict the outcome of neurological and neurosurgical patients. To determine an optimal clinical model we will undertake a multivariable regression analysis to assess which variables are independently associated with outcome. Multiple regression models with a minimum of 10 to 15 observations per predictor variable reveal good estimates. We will evaluate 18 predictors in our multivariate analysis. Therefore, we aim to include a minimum sample size of 180 patients (for 10 observations per predictor) to 270 (for 15 observations per predictor) and a maximum sample size of 360 patients (for 20 observations per predictor).

**Significance:** Despite the frequent occurrence and the poor outcomes of serious disorders of sodium balance, few controlled data are available to guide the clinician. A better diagnostic approach to determine the etiology of hyponatremia should improve patient management. Copeptin as a prognostic marker in neurological and neurosurgical patients could become an innovative tool to guide early treatment decisions, discharge from the stroke unit and application of interventions.

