**2. RESEARCH PLAN**

**2.1 Introduction**

Disorders of serum sodium are the most common electrolyte disorder in hospital practice [1] and represent a significant healthcare burden [2]. Mild hyponatremia (i.e. plasma sodium 130-135mmol/l) is found in as many as 15-30% of hospitalized patients [3-6]. More severe hyponatremia (plasma sodium <130mmol/l) is seen in 1-4 % of inpatients [7]. Hyponatremia in hospitalized patients has a significant mortality ranging from 5% to 50%, depending on severity and acuity of onset as well as comorbidities. Hypernatremia is far less common but mortality ranges from 60 to 75% [8].

The central nervous system (CNS) plays an integral role in the neuroendocrine regulation of sodium and water homeostasis. Hyponatremia is the most common electrolyte disorder encountered in the neurologic intensive care unit [3,9,10]. It is seen in patients with subarachnoidal hemorrhage (SAH) [11], brain tumors [12-14] and ischemic stroke [15-17], complicating their clinical courses [9]. A timely and accurate diagnosis followed by a correct treatment is crucial [18,19]. Differential diagnoses include the syndrome of inappropriate antidiuretic hormone secretion (SIADH), cerebral salt wasting (CSW), hypo- or hypervolemic hyponatremia, and mixed cases [20]. Besides measurement of plasma osmolality and sodium concentration in urine, determination of the extracellular fluid volume remains the most important discriminatory element. However, its prediction based on clinical signs and routine laboratory evaluation has a limited sensitivity and specificity of <50% [21,22]. Accordingly, only 10% of physicians reach the correct diagnosis of the underlying cause of hyponatremia with the routinely used clinical diagnostic algorithms [23]. Thus, there is demand for more reliable parameters to improve the diagnosis of sodium imbalance in patients with CNS disease.

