**2.2 DETAILED RESEARCH PLAN**

**A. Objectives**

The objectives of this trial are to evaluate

1. The diagnostic value of copeptin levels in the diagnosis of water imbalance in patients with stroke and patients undergoing intracranial surgery.
2. The prognostic accuracy of copeptin levels and other biomarkers to predict the clinical outcome in patients with stroke and patients undergoing intracranial surgery.

Specific objectives of the study are:

- - 1. **Diagnostic Study:**

**Hyponatremia** will be defined as serum sodium concentration below 135 mmol/L [31].

Specifically, we aim to investigate whether Copeptin levels can facilitate the differential diagnosis of hyponatraemia. Thereby, we will use a standardized clinical algorithm based on medical history, drug history, clinical assessment of the extracellular fluid volume, and laboratory parameters such as plasma and urine sodium concentration, plasma and urine osmolality, creatinine, uric acid, urea, total protein, albumin, TSH, fT4, T3, blood glucose, urea nitrogen, plasma potassium to evaluate the aetiology of hyponatraemia (**figure 1**). In our cohort, wee expect a prevalence of around 20 % (i.e. around 75 patients of the 350 patients derived from the power calculation, see below) to have hyponatraemia. The etiologies are listed in Figure 1 including the estimated relative contributions and the most frequent diagnosis within the subgroup is underlined.

**Figure 1** Diagnostic algorithm of hypotonic hyponatraemia:

We **hypothesize** that overall, included patients will have moderately but significantly higher copeptin levels (around 5pmol/L) as compared to healthy controls (4pmol/L). In patients with hyponatraemia, copeptin levels will be lower as compared to patients without hyponatraemia, however, with a wide range (1.7pmol/L (detection limit) to 15pmol/L). Analysing the subgroup of patients with hyponatraemia, we assume that in patients with SIADH, copeptin levels will be markedly increased (i.e. 12pmol/L), moderately increased (8pmol/L) in hypovolemic hyponatraemia and suppressed in hypervolemic hyponatraemia (<2pmol/L). Importantly, we anticipate to identify SIADH as a co-factor also in some patients with “typical” hypervolaemic and hypovolemic hyponatremia, where ADH disturbances have been neglected previously due to the incapability to assess circulating ADH levels.

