**Statistical Analyses**

Copeptin levels will be assessed in a blinded batch analysis upon completion of the plasma asseveration.

Discrete variables will be expressed as counts (percentage) and continuous variables as means ± standard deviation (SD) or median (interquartile range), unless stated otherwise. First, the overall prevalence of hyponatraemia in neurological and neurosurgical patients will be assessed. Frequency comparison will be done by chi-square test. Two-group comparison of normally distributed data will be performed by Students t-test. For multigroup comparisons, one-way analysis of variance with least square difference for posthoc comparison will be applied. For data not normally distributed, the Mann-Whitney-U test is used if only two groups are compared. The Kruskal-Wallis one-way analysis of variance with Bonferroni’s multiple posthoc test will be used if more than two groups were being compared.

Furthermore we will do a correlation analysis of copeptin levels with sodium levels, serum osmolality and other diagnostic laboratory parameters. Correlation analyses will be performed by using Spearman rank correlation. Levels that are non-detectable will be assigned a value equal to the lower limit of detection for the assay. All testing will be two-tailed and P values less than 0.05 were considered to indicate statistical significance. Scatterplot data will be shown with GraphPad Prism®, Version 4.00 for Windows (GraphPad Software, San Diego California, USA).

We will then compare the diagnostic accuracy of Copeptin levels with other potential biomarkers for sodium imbalance, e.g. atrial natriuretic peptide (ANP) and B-type natriuretic peptide (BNP). The ability of Copeptin to foresee sodium disbalance before it becomes evident by laboratory analysis will be assessed. Therefore we will correlate Copeptin levels with sodium level changes over time.We will construct receiver operating characteristic (ROC) curves and determine the areas under the receiver operating characteristic curve (AUC). The sensitivity and specificity to predict the correct diagnosis of hyponatraemia will be determined, based on the above standardized algorithm [32]. This ascertainment will be done retrospectively on the basis of the review of the complete patient charts by two study investigators, blinded to each other’s diagnosis. Discordant cases will be mutually discussed and resolved. Patients will be managed as usual according to the state of the art treatment.

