**Overall, the hypotheses are the following**:

1. Copeptin will be a new accurate diagnostic tool to facilitate the differential diagnosis of the etiology of sodium imbalance. Copeptin will have a higher diagnostic accuracy as compared to the routinely used clinical assessment of the extracellular fluid volume by physical examination and laboratory parameters. If copeptin is found to be an accurate tool, we aim to validate our findings in a future intervention study, with the aim to improve the management of neurosurgical and neurological patients with sodium imbalance based on copeptin levels.

2. Copeptin will be a reliable prognostic factor and high-quality predictor for the clinical outcome (i.e. mortality, length of stay in ICU, discharge from ICU, length of hospitalization, clinical outcome within the first week and after three months) of neurological and neurosurgical patients.

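### The reference diagnosis is built from the routine assessments that hypothesis 1 says copeptin will beat, so the comparison is biased towards those assessments

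*Protocol*

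**What the plan says.** **Reference.** The Statistical Analyses part of the diagnostic study (Protocol, section 2.2) says: "The sensitivity and specificity to predict the correct diagnosis of hyponatraemia will be determined, based on the above standardized algorithm". The diagnosis is ascertained retrospectively by "review of the complete patient charts by two study investigators", who are blinded to each other and resolve disagreements by discussion.

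**What the algorithm contains.** Section 2.2 A, Objectives: "we will use a standardized clinical algorithm based on medical history, drug history, clinical assessment of the extracellular fluid volume, and laboratory parameters", followed by a list that includes plasma and urine sodium, osmolality and uric acid. Copeptin, ANP and BNP are not on the list. Hypernatraemia is also to be classified by a clinical and laboratory algorithm.

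**What copeptin should beat.** The overall hypotheses expect "higher diagnostic accuracy as compared to the routinely used clinical assessment of the extracellular fluid volume by physical examination and laboratory parameters". The synopsis has a similar version: "Copeptin will improve the diagnostic accuracy to diagnose sodium imbalances as compared to routinely used markers".

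**What the protocol thinks of the comparator.** Section 2.1 says that predicting extracellular volume from clinical signs and routine laboratory evaluation has "limited sensitivity and specificity of <50" per cent.

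**What copeptin is expected to add.** Section 2.2 A: "we anticipate to identify SIADH as a co-factor also in some patients" whose hyponatraemia looks typically hypervolaemic or hypovolaemic.

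**The concern.** A test's accuracy is only as meaningful as the reference it is scored against. Here the reference is formed from the volume examination and laboratory values that also serve as the comparator. Their errors pass into the reference and are then scored as correct. Where copeptin is right and the routine assessment is wrong, copeptin is marked wrong.

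This bears on the very benefit the protocol hopes for. Suppose copeptin signals SIADH in a patient whom the algorithm labels hypovolaemic or hypervolaemic. Against this reference, that result counts as a copeptin false positive. A true gain over routine practice would lower copeptin's measured accuracy.

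At stake is the claim of higher diagnostic accuracy, on which the protocol would build a later intervention study.

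**Working it through.** The protocol gives no target accuracy or power for the diagnostic hypothesis, so it has no figure to reproduce. Every accuracy below is an assumption, used to show direction and possible size.

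**1. Comparator = the whole algorithm.** Take a binary diagnosis (SIADH or not) with symmetric, independent errors. Let *a* be the true accuracy of the algorithm and *c* that of copeptin.

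- Measured accuracy of the algorithm against itself: 1.00, whatever *a* is.
- Measured accuracy of copeptin: *ac* + (1 − *a*)(1 − *c*).
- *a* = 0.70, *c* = 0.95: 0.665 + 0.015 = 0.68.
- *a* = 0.90, *c* = 0.95: 0.855 + 0.005 = 0.86.
- *c* = 1.00: copeptin measures *a*, for example 0.70 or 0.90.

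Copeptin can at best tie.

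**2. Comparator = one routine component (bedside volume assessment).** Suppose the reference follows the bedside finding in a share *s* of cases and otherwise follows other chart information. Assumed true accuracies: bedside 0.60, other chart information 0.85, copeptin 0.90. Errors are independent and prevalence is 50%.

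- Bedside measured: *s* + (1 − *s*)(0.60 × 0.85 + 0.40 × 0.15) = *s* + 0.57(1 − *s*).
- Copeptin measured: *s*(0.60 × 0.90 + 0.40 × 0.10) + (1 − *s*)(0.85 × 0.90 + 0.15 × 0.10) = 0.58*s* + 0.78(1 − *s*).

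| Share *s* | Bedside | Copeptin |
|---|---|---|
| 0 | 0.57 | 0.78 |
| 0.25 | 0.68 | 0.73 |
| 0.50 | 0.79 | 0.68 |
| 0.75 | 0.89 | 0.63 |
| 1 | 1.00 | 0.58 |

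The lines cross where 0.57 + 0.43*s* = 0.78 − 0.20*s*, so *s* = 0.21/0.63 = 1/3. With bedside accuracy of 0.50 or 0.70 the reversal also falls between *s* = 0.25 and *s* = 0.50. In truth copeptin is far better in every row, yet it ranks second once the reference leans on the bedside finding in more than about a third of cases.

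**3. Reference error alone.** For an error-free test, apparent sensitivity is the reference's positive predictive value, *p*Se/[*p*Se + (1 − *p*)(1 − Sp)]. Apparent specificity is the reference's negative predictive value. Assume a SIADH share *p* = 0.33.

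- Se = Sp = 0.70: 0.231/(0.231 + 0.201) = 0.535; 0.469/(0.469 + 0.099) = 0.826.
- Se = Sp = 0.80: 0.264/(0.264 + 0.134) = 0.663; 0.536/(0.536 + 0.066) = 0.890.

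This third calculation measures attenuation from an imperfect reference. It would affect ANP and BNP too and does not depend on incorporation. Steps 1 and 2 show the effect of incorporation.

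**The case against.** The strongest reply is that reference and comparator are not identical. The reference is a two-reader consensus on the full chart and adds medical and drug history. The comparator is volume examination with laboratory parameters, or simply routine markers. That stands: a tie is forced only against the whole algorithm, and step 2 shows copeptin ahead of a component when the reference relies on it little. A reader might infer that hypothesis 1 cannot be confirmed whatever the data show, but the text does not support that. The part about facilitating the differential diagnosis can also be examined as agreement with the algorithm.

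Three other inferences go too far.

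- **That the protocol itself puts the reference below 50%.** That figure concerns prediction of extracellular volume. It is not the accuracy of the full algorithm or of a two-reader consensus, so it sets no ceiling on the reference.
- **That copeptin will be used to relabel cases as SIADH.** The co-factor sentence states an expected finding and sets no classification rule. Copeptin is not an input to the algorithm and is assayed late, in a blinded batch. What remains is narrower: the readers are described as blinded only to each other, and the timing of chart review relative to the assay results is not stated.
- **That ANP and BNP are the only planned comparators.** They are given as examples, and further paired comparisons may sit in an analysis plan that is not shown. Comparison with them is free of incorporation, though it inherits reference error.

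The study is also exploratory, its sample size rests on the prognostic question, and the protocol intends later validation. This lowers the severity but leaves the conflict in place: the protocol itself fixes both the hypothesis and the reference, and an analysis method cannot separate them afterwards.

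**Conclusion.** The concern holds as incorporation bias. The comparator's core inputs are built into the reference, and the protocol names no independent element for it. Three consequences follow: superiority over the algorithm as a whole cannot be shown; the ranking against single routine components can reverse; and SIADH that copeptin finds in apparently typical hypovolaemic or hypervolaemic cases would be scored as copeptin error.

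The size is not known from the documents. The figures in the working rest on assumed accuracies, independent errors and an assumed SIADH share. The protocol's own estimated contributions are in a figure that is not shown.

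The plan as written cannot soundly support a claim of higher diagnostic accuracy, but it can still estimate agreement with the routine algorithm. The prognostic objective is untouched. This should be fixed before the diagnostic result is reported as a comparison of accuracy.

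**What to change.** Choose one of two routes.

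1. **Restate the aim.** Word hypothesis 1, in the synopsis and in the overall hypotheses, as agreement of copeptin with the routine algorithm, and drop the claim of higher accuracy. This costs only wording.
2. **Separate the two roles.** Define the routine index diagnosis as the algorithm applied to data available at the first sodium below 135 or above 145 mmol/L. Have the same two readers adjudicate the reference after discharge from the complete chart, relying on the later sodium course and the response to whatever treatment was given, and not on the index algorithm as decision rule. Step 3 of the participant management section already collects fluid treatment and routine laboratory results. Allow an indeterminate category. Compare copeptin and the routine markers against this reference in paired analyses. Acknowledge residual incorporation, because the chart still holds the routine items.

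Under either route, state that the readers are masked to copeptin, ANP and BNP and that diagnoses are locked before assay results are released. Report SIADH as a co-factor descriptively.

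The second route costs protocol wording and an adjudication form, with the same readers and charts. Its drawback is that some cases will be indeterminate.

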**2.2.2. Prognostic Study:**

We will assess the prognostic value of copeptin dependent or independent of sodium imbalance.

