**Prognostic question in patients with stroke**

In stroke patients we will evaluate the prognostic value of Copeptin -levels - dependent or independent of sodium imbalance- to predict mortality, ICU stay, length of hospitalization; and morbidity (i.e. outcome after 90 days), as assessed by the National Institute of Health and Stroke Scale (NIHSS, [33], **Appendix 1**) on admission and at day 5, the Barthel index [34] (**Appendix 2**) and Ranking scale [35] (**Appendix 3**) at day 5 of the hospitalization and after a follow-up of 3 months by telephone interview with the patient or if not possible with the nearest relative or health care provider. Further other biomarkers, such as MR-pro ANP, BNP and Troponin will be assessed.

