**Statistical Analyses**

Basic statistical analyses will be performed as described in the diagnostic study. We will evaluate 18 known predictors (i.e. *age; sex; clinical features* (NIHSS or GCS), *important comorbidities* (coronary artery disease, heart failure, atrial fibrillation, hypertension on admission, previous TIA/Stroke, renal disease, dementia, diabetes); *location of the lesion* (LACS etc.); *stroke subtype by the TOAST criteria*; *therapies* (thrombolysis); *laboratory parameters (*baseline glucose level on admission [46-50], CRP); *body temperature*; *smoking histo*ry), and copeptin levels in our multivariate analysis. All variables will first be tested one by one against the dependent variable unfavorable outcome (defined either as Barthel index <85 or modified Ranking scale 3 to 6) for the presence of a significant association. Only variables significantly associated with the outcome will be assessed in a multivariate model performed separately for each parameter.

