**C Procedures**

**Baseline data collection (Appendix 6)**

Access to data of all eligible patients that are not included into this study is important to avoid a selection bias. Thus, we will collect baseline data and information on inclusion and exclusion criteria in all eligible patients irrespective whether they are or are not included into the study. This will allow the comparison of baseline data of eligible patients who consented to participate with those who did not.

Baseline data collection in patients will be collected by the investigators and contain

a) age

b) gender

c) BMI

d) Medical history items: actual history that preceded the hospitalization; ABCD score in patients with transient ischemic attack (Rothwell [38]**Appendix 7**); family history; relevant co-morbidities also assessed by the charlson index [39] (**Appendix 8**) (i.e. hypertension, previous stroke, previous TIA, ischemic heart disease, atrial fibrillation, diabetes mellitus, renal and liver dysfunction, congestive heart failure, dyslipidemia; comorbidities with the risk of hyponatremia (severe hypothyroidism, glucocorticoid insufficiency, neoplasm, HIV infection); smoking history (pack-years) and status (pack per day); current medication; alcohol consumption (glass and grams per day); time from onset of symptoms to admission.

e) Place of residence: i.e. independent living, defined as living at home or in an old people’s home with or without support of the family circle and/or professional care (the family circle consists of the spouse and/or other important persons who live together with the patient; dependent living, defined as nursing home long-stay department, other hospital [40].

f) Clinical items: physical examination including neurological status, NIHSS (to assess the severity of stroke in stroke patients) and Glasgow Coma scale (GCS [41]); blood pressure, pulse rate, weight, volume status (including skin turgor, jugular venous distension, auscultation, if available flow sheet of fluid intake and loss), body temperature; in neurosurgical patients intracerebral pressure if performed within the routine clinical management.

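### The protocol asks whether copeptin predicts outcome independently of sodium imbalance, but its outcome model contains no sodium term

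*Protocol*

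**What the plan says.** The aim appears in three places in the protocol.

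- Synopsis, second study hypothesis: "Copeptin will be a reliable prognostic tool, dependent or independent of sodium imbalance, to predict short-term" and medium-term outcome.
- Section 2.2.2, opening sentence: "We will assess the prognostic value of copeptin dependent or independent of sodium imbalance".
- Prognostic question in patients with stroke: "dependent or independent of sodium imbalance- to predict mortality, ICU stay, length of hospitalization" and 90-day morbidity.

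The model is set out in the Statistical Analyses part of section 2.2.2: "We will evaluate 18 known predictors". A full enumeration follows, and copeptin is then added. The comorbidities are "coronary artery disease, heart failure, atrial fibrillation, hypertension on admission, previous TIA/Stroke, renal disease, dementia, diabetes". The laboratory items are "baseline glucose level on admission [46-50], CRP". Section E repeats the same 18 and derives the sample size from them. A variable reaches the multivariable model only if it is significant on its own, and section E adds stepwise logistic regression.

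Sodium itself is available. Serum electrolytes are part of the baseline laboratory tests, and routine chemistry is followed during the stay (section C).

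**The concern.** To say that a marker predicts outcome independently of some condition, that condition has to be in the model or the analysis has to be split by it. Here it is neither.

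The protocol itself links sodium to both sides. The diagnostic study expects copeptin to differ by sodium status and by aetiology. The introduction ties sodium disorders to death, with hyponatraemia mortality of 5% to 50%, and adds: "Hypernatremia is far less common but mortality ranges from 60 to 75" per cent. A copeptin coefficient from the planned model could therefore carry some of the prognostic weight of sodium disturbance, and the model gives no means of telling how much.

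At stake is one claim, the independence of copeptin from sodium. Whether copeptin predicts outcome at all is a separate matter.

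**Working it through.** **1. Is sodium in the list?** Counting the enumeration: age, sex, NIHSS or GCS (3); comorbidities (8); lesion location, TOAST subtype, thrombolysis (3); glucose, CRP (2); body temperature, smoking (2). Total 3 + 8 + 3 + 2 + 2 = 18. None is sodium or osmolality.

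**2. Is there an unlisted slot?** The protocol's sample sizes are 18 × 10 = 180, 18 × 15 = 270 and 18 × 20 = 360, all exact. The count leaves no room for an unnamed predictor, nor for copeptin, which is the 19th.

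**3. Is the question answered elsewhere?** The further prognostic factors (natriuretic peptides, troponin, procalcitonin, IL-6 and others) do not include sodium. Copeptin and sodium are analysed together only in the diagnostic study, by Spearman correlation and by ROC curves for the sodium diagnosis. Neither involves clinical outcome.

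**4. Can the sample carry a sodium term?** Attainable size: 480 × 0.80 × 0.90 = 345.6, given as about 350. Candidates: 18 + 1 (copeptin) + 2 (three-level sodium) = 21, and 350 / 21 = 16.7.
- Counting categories strictly, lesion location has four levels (3 df) and TOAST five (4 df), so the list uses 16 + 3 + 4 = 23 df. With copeptin and sodium that is 26, and 350 / 26 = 13.5, within 10 to 15.
- At the minimum of 180 patients the ratio is 180 / 21 = 8.6, but copeptin alone already brings it to 180 / 19 = 9.5.
- If the model were fitted in stroke patients only, 300 × 0.80 × 0.90 = 216 and 216 / 21 = 10.3.
- These ratios count patients, as the protocol does. It gives no event rate, so events per variable cannot be computed.

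**5. How large could the bias be?** Simulated data sets of 350 patients had no copeptin effect within sodium category.
- From the protocol: 20% hyponatraemic (70) and 10% hypernatraemic (35), leaving 245; copeptin around 5 pmol/L overall, used here for normal sodium; 12, 8 and below 2 pmol/L for the three hyponatraemia aetiologies; 1.7–2, 8 and 12 for those of hypernatraemia. The protocol's own counts of 75 and 45 do not match its percentages.
- Assumed: log-SD 0.5; unfavourable outcome in 30/40/65% or 30/50/70% (normal/hypo/hyper); aetiology shares, because the figures giving them are not shown.
- Model: logistic regression of outcome on log copeptin, with or without sodium category.

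The protocol expects lower copeptin in hyponatraemia than without it. The shares below give a hyponatraemic geometric mean of about 3.5 pmol/L. False-positive rates at 0.05, without sodium:

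| Hyponatraemia: SIADH / hypovolaemic / hypervolaemic | Hypernatraemia: low / middle / high copeptin | 30/40/65% | 30/50/70% |
| --- | --- | --- | --- |
| 20/20/60 | equal | 5.5% | 6.3% |
| 15/25/60 | 20/40/40 | 7.6% | 4.9% |
| 20/20/60 | 10/45/45 | 11.2% | 8.4% |

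The median spurious odds ratio per doubling was 0.97 to 1.09. Across repeat runs with shares of this kind the rate is about 6–12%; the 4.9% cell shows that it can also be nil. Equal shares in both groups give 7% and 9%. If high-copeptin aetiologies dominate (hyponatraemic geometric mean about 8.9 pmol/L), it is about 23% and 44%. With the three-level sodium term it is about 3–6% throughout.

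**The case against.** The strongest reply has four parts.

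First, the bias is small on the protocol's own expectations. Copeptin is expected to be low in hyponatraemia and high in hypernatraemia. If both groups do worse, the two biases pull in opposite directions and partly cancel. This stands. A reader might infer from the 23–44% figures that a positive copeptin result would probably be spurious. The document does not support that, because those figures need copeptin in hyponatraemia to be well above normal, contrary to the diagnostic hypothesis.

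Second, the simulated model holds copeptin alone, whereas the plan also considers stroke severity, age, heart failure, renal disease, glucose and CRP, which may absorb part of the sodium association. The mortality figures in the introduction concern hospitalised patients in general, not three-month function in this cohort. Both points stand, and they are further reasons not to rest the case on size.

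Third, copeptin mirrors ADH, which regulates sodium, so a sodium disturbance may lie downstream of copeptin, as in SIADH. Leaving sodium out does not spoil prediction as such. This stands too; only the claim of independence is left unsupported.

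Fourth, the wording may mean no more than whether or not sodium is disturbed, and objective 2, the neurosurgical paragraph and the later restatement of the hypotheses omit it. The looser reading does not help, since it too needs a stratified or adjusted outcome analysis. The omission elsewhere narrows the point but leaves three explicit statements of the aim.

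Nor is this a detail left to an analysis plan: the protocol names the predictors and sizes the study on their number.

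**Conclusion.** The point holds as a mismatch between a stated question and a stated model. This rests on the text and the count of 18, and needs no assumption. Its likely numerical effect, a false-positive rate of about 6–12% against a nominal 5%, depends on assumed outcome risks, aetiology shares and spread of copeptin.

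Two stronger readings should be resisted. A reader might infer that any copeptin effect would be entirely due to sodium. That is possible, but nothing in the document predicts it. A reader might also add pre-admission dependency, since "Place of residence: i.e. independent living" is recorded at baseline and the outcome is functional. No stated aim concerns independence from prior dependency, however. Dementia and previous stroke or TIA are already candidates, and the recorded variable counts home living with professional care as independent. That is a modelling preference, not a contradiction in the plan.

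The study describes itself as exploratory, the data are collected, and the repair is one added term. This should be fixed before analysis; it is not a fatal defect.

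**What to change.** In the Statistical Analyses part of section 2.2.2, and likewise in section E:

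- Add serum sodium as a three-level category (below 135, 135–145, above 145 mmol/L, the protocol's own limits), taken at the time of the copeptin sample used in the model. Categories are preferable to a linear term because both extremes may carry risk.
- Force this term into the copeptin outcome model. Exempt it from the univariable screen and from stepwise removal; otherwise a non-significant sodium term would drop out and the question would again go unanswered.
- Report the copeptin odds ratio without and with the sodium term. A copeptin-by-sodium interaction is optional and should be labelled exploratory.

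The cost is wording and 2 degrees of freedom (more if the interaction is fitted). No extra data are needed. At about 350 patients no comorbidity has to be dropped to make room.
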